#### Inclusion criteria

Conformity with the diagnostic criteria of idiopathic PD according to the 2015 Movement Disorder Society (MDS) criteria [3]Patients that are classified as 1–3 according to the Hoehn and Yahr scale [44]Age of 45–70 years and primary school education level and aboveThe drug effect was stable for more than 2 weeks without adjustment and no DBS surgery was performedThose who can walk without assistance (including assistive devices) and need no help from others in daily lifeThose who voluntarily sign the informed consent form and confirm that they will be able to complete the treatment

#### Exclusion criteria

The diagnosis is unclear or suspected of Parkinson’s syndrome (such as vascular, drug-induced, and post-infection Parkinson’s syndrome), multiple system atrophy, progressive supranuclear palsy, etc.Patients with cognitive, motor, speech, and other impairments caused by other nervous system diseasesA history of epilepsy or other contraindications to tACSSubjects who are unwilling or unable to participate in MRI examinations (such as those with claustrophobia or non-MRI-compatible implants in the body)Serious concomitant diseases such as heart, lung, liver and kidney insufficiencyThose who are participating in other clinical trials or are going to undergo DBS surgery or participate in other clinical trials in the next 12 monthsPatients who are unable to cooperate to complete the treatment or examinationPatients who are not willing to sign the informed consent form

#### Dropping criteria

Patients who revoke their informed consentPatients who discontinued treatment due to various factors

### Who will take informed consent? {26a}

Before the baseline assessment, all participants will be required to provide a written informed consent form. Participation will be voluntary, and patients may withdraw from the study at any time. Caregivers of potential participants will need to give informed consent prior to the allocation of time points. The informed consent process will ensure that participants and their caregivers are fully aware of the study’s objectives, activities involved, as well as its potential benefits and risks. Participants were encouraged to ask any questions they might have had during this process. Ultimately, it is up to the caregivers or participants themselves to decide whether or not they wish to participate in the study after being provided with comprehensive information. All data collected will be anonymized for confidentiality purposes. Multiple communication channels will be established in order to maintain close contact with participants.

### Additional consent provisions for collection and use of participant data and biological specimens {26b}

We will confirm with the participants if their data may be used.

## Interventions

### Explanation for the choice of comparators {6b}

The application of tACS as a non-invasive brain stimulation (NIBS) technique in clinical treatment is well-established. In this study, the inclusion of sham-tACS + MIRT in the control group served to elicit a placebo effect, with the only discernible distinction between the tACS + MIRT group and sham-tACS + MIRT being the presence or absence of electrical current. (Further details regarding this intervention can be found in the “Intervention description {11a}” section).

### Intervention description {11a}

After the initial baseline assessment (days 1–2), patients will be administered tACS + MITR or sham-tACS + MIRT for a consecutive period of 10 days (days 3–12).

#### tACS + MIRT group and sham-tACS + MIRT group

During each treatment session, patients will receive tACS or sham tACS stimulation for 40 min twice a day. The treatment duration was standardized for each day (40 min per session, twice daily for 10 days, totaling 20 sessions). Patients will receive a 10-day MIRT program based on tACS treatment, which includes four distinct rehabilitation exercises per day with each session lasting 30–60 min.

Participants were comfortably seated on reclining chairs to receive FDA-approved tACS from Nexalin Technology, Inc. The administration of tACS was carried out by trained medical professionals following standardized instructions. This trial utilized two tACS devices, one sham and one active, which were identical in terms of size, color, appearance, weight, and odor. Each participant was consistently assigned to the same device throughout the entire intervention.

Patients were instructed to consume water prior to the intervention, maintain a state of relaxation or even sleep, and minimize communication with medical personnel. Three Nexalin conductive electrodes were positioned above the head according to the 10/20 international placement system, with a 4.45 × 9.53 cm electrode placed on the forehead corresponding to Fpz, Fp1, and Fp2. Two 3.18 × 3.81 cm electrodes were placed on each side in the mastoid region. The tACS stimulation waveform consisted of ramp-up and ramp-down periods lasting for 180 s and 12 s respectively. It was a square wave with an average amplitude of 15 mA and was equally distributed from the frontal region to the mastoid areas (amplitudes are reported as zero-to-peak). All participants received a total of twenty sessions involving either true or sham stimulation at a frequency of 77.5 Hz and intensity of 15 mA, respectively. Sham tACS had no active stimulation.

#### MIRT procedure

I.Physical therapy. It involves warm-up activities followed by active and passive stretching and flexibility training. The physical therapist will conduct session in groups of four for a duration of 40 minutes.II.Gait balance training. C-MiLL (Motek, Amsterdam/ Culemborg, Netherlands) and Balance Tutor (Meditouch, Netanya, Israel) will be utilized to enhance balance and gait. Patients will undergo 30-min training sessions once per day.III.Aerobic training. Patients will engage in a 30-min aerobic workout using an upper and lower limb trainer (T5XR; Nustep, Ann Arbor, MI, USA).IV.Speech therapy. The speech therapist will conduct one-hour group sessions of 4 patients.

Throughout the trial, we will have the option to modify parameters or discontinue treatment entirely in response to any adverse events that may arise. Physicians and therapists will document any such events in writing within the Electronic Data Capture (EDC) system for review by the study team. Additionally, falls, injuries, and other harmful incidents must be reported in accordance with regulations set forth by Beijing Rehabilitation Hospital affiliated with Capital Medical University.

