### Trial design {8}

The study will be a double-blind, randomized, placebo-controlled trial. The present protocol follows the Standard Protocol Items Recommendations for Interventional Trials (SPIRIT) guidelines and fulfills the SPIRIT checklist [44]. Our hypothesis is that tACS combined with MIRT is superior in terms of efficiency and effectiveness compared to MIRT alone for treating PD. Each patient’s participation in the study will last for 26 weeks, including baseline evaluation (T0), a 10-day intervention period, and assessments at the end of intervention (T1), as well as 4 weeks (T2), 12 weeks (T3), and 24 weeks (T4) post-intervention. Please refer to Fig. 1 for details regarding patient visits and follow-up schedule. Additionally, Fig. 2 provides an overview of all interventions and outcome measures in accordance with SPIRIT 2013 guidelines [45] (Additional file 1).

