### Criteria for discontinuing or modifying allocated interventions {11b}

The intervention will be terminated upon the patients’ request.

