### Sample size {14}

PASS11 software was used to calculate the sample size. According to the previous literature [65, 66], which includes the results of PDQ-39 in individuals with Parkinson’s disease, and in combination with this experiment, we designed a ratio of 1:1 between the tACS + MIRT group and Sham-tACS + MIRT group. The statistical power was set at 0.9, with a significance level (α) of 0.05. Based on these parameters, the required sample size for each group was calculated as 27. Considering an attrition rate of 10%, it was determined that each group would need a total of 30 patients, resulting in a combined total of 60 patients.

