## Data collection and management

### Plans for assessment and collection of outcomes {18a}

The following data will be collected at baseline: gender, age, occupation, educational level, current medication status, and detailed physical and neurological examinations. Inclusion and exclusion criteria will be evaluated. PDQ-39 assessments will be conducted at T0, T2, T3, and T4. MDS-UPDRS III [49, 55], Mini-BES test [50, 56], 6MWT [51, 57], NMSS [52, 58], MoCA [53, 59], and HAMD, as well as other motor symptom scales and non-motor symptom scales, will be assessed at T0, T1, T2, T3, and T4 respectively. MRI and EEG scans will be evaluated at T0 and T1. Levodopa equivalent daily dose (LEDD) data will be collected at T0, T1, T2, T3, and T4. All these assessments will be conducted in a double-blind manner by raters who were unaware of the treatment administered to the patients. At T0 and T1, various safety indicators including blood routine, urine routine, stool routine, liver and kidney function tests, electrocardiogram readings, and other relevant parameters will be evaluated. Any adverse events occurring during the study will be documented. Participants will be asked for their consent regarding the use of their data if they choose to withdraw from the trial. Additionally, participants must obtain permission from the research team to share their pertinent information with university personnel involved in the study or relevant regulatory authorities. Prior to commencing the study, investigators will undergo standardized training on data collection strategies as well as guidelines for utilizing different scales to assess outcomes. Throughout the trial period, professionally trained researchers will collect data to ensure impartiality. In case subjects experience an “on–off” phenomenon during treatment response fluctuations; separate data collection sessions will take place during both “on” and “off” periods for subsequent comparison.

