### Methods in analysis to handle protocol non-adherence and any statistical methods to handle missing data {20c}

The intention-to-treat (ITT) analysis will be the primary analysis of this study, with per-protocol (PP) analysis as a secondary analysis in case patients were unable to receive the intervention due to issues related to the intervention itself, such as adverse effects, difficult administration, or adherence problems. Missing data will be handled using the last observation carried forward (LOCF) method. Sensitivity analyses will be conducted if there are imbalanced losses to follow up or excessive attrition.

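### Stopping treatment counts as dropping out, so under LOCF a dropped discontinuer enters the primary analysis with a PDQ-39 change of exactly zero

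*Protocol article*

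**What the plan says.** - **Dropping criteria.** Two grounds are listed side by side: revoking consent, and stopping treatment for whatever reason. The section does not define what dropping entails.
- **MIRT procedure.** During the trial, "we will have the option to modify parameters or discontinue treatment entirely in response to any adverse events that may arise".
- **Criteria for discontinuing or modifying allocated interventions {11b}.** "The intervention will be terminated upon the patients’ request".
- **Intervention description {11a}.** Treatment runs on days 3 to 12, directly after the baseline assessment.
- **Trial design {8}.** After the end-of-intervention visit (T1), assessments follow "as well as 4 weeks (T2), 12 weeks (T3), and 24 weeks (T4) post-intervention".
- **Plans for assessment and collection of outcomes {18a}.** "PDQ-39 assessments will be conducted at T0, T2, T3, and T4". There is no PDQ-39 at T1.
- **Methods for non-adherence and missing data {20c}.** "The intention-to-treat (ITT) analysis will be the primary analysis of this study", with a per-protocol analysis as secondary when patients could not receive the intervention, adverse effects being one example. Then: "Missing data will be handled using the last observation carried forward (LOCF) method". Sensitivity analyses are promised if losses to follow-up are imbalanced or attrition is excessive.

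**The concern.** An ITT estimate describes the effect of assignment only if patients who stop treatment are still measured. Here, stopping treatment is placed in the same class as leaving the study, and the stated method for the resulting gaps is LOCF. Because of the PDQ-39 schedule, the only value available to carry is the baseline one, so the primary outcome of such a patient is fixed at no change.

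That value is hard to defend. Both arms receive MIRT, and the Discussion cites randomised studies in which MIRT improved quality of life, so a patient who had part of the programme may well have gained something. Stopping may also differ by arm. Active stimulation is 15 mA, sham delivers no current, and the adverse-event section names headache, site pain and seizures as possible events. The protocol gives no stopping rates, so unequal stopping is a possibility rather than a forecast.

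**Working it through.** **Step 1: timing.** Treatment occupies days 3 to 12. The PDQ-39 is taken at T0 and next at T2, four weeks after the intervention. Every treatment discontinuation therefore precedes the first post-baseline PDQ-39. If the patient is then no longer assessed, LOCF carries T0, and the change is T0 − T0 = 0 at T2, T3 and T4. This needs no assumption beyond the patient being dropped from follow-up.

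**Step 2: the plan's own figures.** Sample size {14} gives 27 per group and 10% attrition: 27 / 0.9 = 30 per group, which reproduces. The 27 itself cannot be reproduced, because the article states neither an effect size nor an SD.

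**Step 3: size, under assumptions not in the protocol.**
- D = 4.72 points, the tACS benefit, set equal to the improvement threshold quoted under Primary outcome measures.
- s = 4.72 points, the MIRT gain in both arms (range 0 to 9.44).
- r, the gain a stopped patient actually has at follow-up, between 0 and s and the same in both arms. Stopped tACS patients keep none of D.
- f_A and f_S, the shares stopping in the tACS and sham arms. All are dropped.

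Formulas for the between-arm difference:
- LOCF: (1 − f_A)(s + D) − (1 − f_S)s
- Followed up: (1 − f_A)(s + D) + f_A·r − [(1 − f_S)s + f_S·r]
- LOCF minus followed up: (f_S − f_A)·r

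For 3 of 30 tACS patients and no sham patient stopping (f_A = 0.10, f_S = 0):
- LOCF: 0.9 × 9.44 − 4.72 = 3.78
- Followed up, r = s: 3.78 + 0.1 × 4.72 = 4.25
- Followed up, r = s/2: 3.78 + 0.1 × 2.36 = 4.01
- Followed up, r = 0: 3.78, the same as LOCF

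The other cases use the same formulas:

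| Stopped tACS / sham (of 30 each) | LOCF | Followed up, r = s | Followed up, r = 0 |
|---|---|---|---|
| 3 / 0 | 3.78 | 4.25 | 3.78 |
| 1 / 0 | 4.41 | 4.56 | 4.41 |
| 3 / 3 | 4.25 | 4.25 | 4.25 |
| 0 / 3 | 5.19 | 4.72 | 5.19 |

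The last row is 9.44 − 0.9 × 4.72 = 5.19. It shows that the error can also run upwards if sham patients stop more often. Over s = 0 to 9.44 in the 3 / 0 case, LOCF gives 4.25 to 3.30, while follow-up with full retention stays at 4.25.

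**Step 4: power, same assumptions.** The plan states: "The statistical power was set at 0.9, with a significance level (α) of 0.05". Taking the test as two-sided, 27 per arm implies a standardised effect of 0.899, hence an SD of 4.72 / 0.899 = 5.25. With 30 per arm and that SD held fixed, 4.25 points (0.81 SD) has about 87% power and 3.78 points (0.72 SD) about 78%. If stopped patients retain none of the MIRT gain, follow-up gives the same 3.78 and there is no power difference to attribute to LOCF.

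**The case against.** Four points on the other side carry weight.

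- **The two stopping provisions do not conflict.** A reader might infer that stopping for adverse events (MIRT procedure) contradicts section {11b}, which names the patient's request. It does not: {11b} never says that this is the sole ground. The adverse-event option is normal safety practice.
- **Exclusion from ITT is not stated.** A reader might infer that dropped patients leave the analysis, so that the ITT label is false. Section {20c} points the other way: it mentions patients who could not receive the intervention because of adverse effects when introducing the per-protocol analysis, which suggests that they remain in the ITT set. Remaining in that set without further assessment is what leads to baseline carried forward.
- **There is a safeguard.** Sensitivity analyses are promised for imbalanced loss, which is the case where the distortion arises. They sit beside the primary estimate, however, and do not change it.
- **The numerical loss is fragile.** A reader might take 4.25 falling to 3.78 as the cost of LOCF. That needs one-sided stopping and full retention of the MIRT gain. Because the safety provision allows treatment to be stopped entirely, MIRT may stop too. With no gain retained, the loss disappears.

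It can also be said that follow-up after stopping is a detail which a condensed article leaves to the full protocol. Silence alone would indeed be no finding. But the article states a dropping rule that pairs stopping treatment with revoked consent, and it states LOCF. No later analysis plan can recover PDQ-39 scores that were not collected.

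**Conclusion.** The point holds in a limited form. The stated dropping rule, the PDQ-39 schedule and LOCF together mean that any discontinuer who is dropped from follow-up contributes a primary change of exactly zero at all three post-baseline times. That depends on reading dropping as the end of assessment. The pairing with revoked consent suggests this, but the protocol does not define it.

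The size and direction of the effect on the treatment comparison are unknown. Under the assumptions above, the LOCF estimate differs from the followed-up one by (f_S − f_A)·r. That is between 0 and −0.47 points when 3 of 30 tACS patients and no sham patient stop, and at most about −0.16 points when 1 of 30 does. It is zero when stopping is equal and retained gain is the same in both arms, and positive when sham patients stop more. The stopping rates, s, D, r and SD are all assumed. This is a cheap improvement to the plan, not a demonstrated failure of the primary analysis.

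**What to change.** 1. Limit the dropping criteria to withdrawal of consent to follow-up. Treat stopping the intervention as treatment discontinuation only.
2. State that patients who stop treatment for any reason complete the PDQ-39 at T2, T3 and T4 and are analysed in their assigned arm. The planned clinic visits or the online follow-up system (Eligibility criteria {10}) can serve for this.
3. Replace LOCF as the primary method. Use either a likelihood-based repeated-measures model that keeps baseline-only patients (T0 among the responses, not only a covariate) or multiple imputation. Keep LOCF as a sensitivity analysis at most.

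The second change matters most. If discontinuers are not measured, a model that assumes data missing at random treats them much like patients in their arm who continued. In the example above that moves the estimate towards 4.72, not towards the effect of assignment.

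The cost is revised wording in the dropping criteria and section {20c}, some extra follow-up contact with patients who have stopped, and somewhat more analysis work. The sample size does not change.

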### Criteria for discontinuing or modifying allocated interventions {11b}

The intervention will be terminated upon the patients’ request.

### Strategies to improve adherence to interventions {11c}

The participants will receive complimentary MIRT treatment, EEG, and MRI examinations to promote adherence to the interventions.

### Relevant concomitant care permitted or prohibited during the trial {11d}

Revised sentence: The concomitant therapies involve the administration of medications such as levodopa and benserazide, in addition to measures aimed at preventing complications. All other non-invasive or invasive brain stimulation interventions, including transcranial direct current stimulation or deep brain stimulation, will be strictly prohibited.

### Provisions for post-trial care {30}

Provisions for ancillary and post-trial care are not relevant to the study.

### Outcomes {12}

#### Primary outcome measures

The primary outcome indicator will be the PDQ-39, which assesses changes in quality of life from T0 to T2, T3, and T4. The PDQ-39 consists of 39 items that are categorized into eight domains: mobility, activities of daily living, emotional, well-being, stigma, social support, cognitions, communication, and bodily discomfort [46]. Patients were instructed to indicate the frequency of occurrence for each corresponding event within the preceding month. The final outcome of the scale encompasses a comprehensive index score, eight sub-core scores, and a weighted percentage reflecting problem severity. Higher scores (ranging from 0 to 100) indicate a greater burden on quality of life (QOL), with − 4.72 and + 4.22 serving as clinically significant thresholds for detecting improvements or deteriorations in QOL among individuals with PD [47]. The PDQ-39 has been translated and validated in multiple languages and cultural settings, making it a recommended tool by the Movement Disorders Society due to its proven effectiveness and stability [48].

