**Methods:**

The present study was a randomized, double-blind trial that enrolled 60 individuals with Parkinson’s disease aged between 45 and 70 years, who had Hoehn-Yahr scale scores ranging from 1 to 3. Participants were randomly assigned in a 1:1 ratio to either the tACS + MIRT group or the sham-tACS + MIRT group. The trial consisted of a two-week double-blind treatment period followed by a 24-week follow-up period, resulting in a total duration of twenty-six weeks. The primary outcome measured the change in PDQ-39 scores from baseline (T0) to 4 weeks (T2), 12 weeks (T3), and 24 weeks (T4) after completion of the intervention. The secondary outcome assessed changes in MDS-UPDRS III scores at T0, the end of intervention (T1), T2, T3, and T4. Additional clinical assessments and mechanistic studies were conducted as tertiary outcomes.

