## Statistical methods

### Statistical methods for primary and secondary outcomes {20a}

SPSS v27.0 software (SPSS Inc., Chicago, IL, USA) will be used for data processing and analysis. Demographic and baseline characteristics of the two groups will be described and analyzed to assess comparability. The PDQ-39 will serve as the primary outcome measure, and an analysis of covariance (ANOVA) model will be employed to estimate the adjusted means of patients’ quality-of-life scores (LSmeans), accounting for baseline differences, as well as calculate 95% confidence intervals for the difference in adjusted means. The count data in the secondary outcome indicators are described by frequency counts. The measurement data are tested for normality using the Shapiro–Wilk method and expressed as mean ± standard deviation if they follow a normal distribution. For non-normally distributed data, they will be described using (P25, P75). Between-group comparisons of motor function, non-motor function-related scale scores, and other secondary indicators between the two groups will be analyzed using appropriate methods based on the type of indicator. Component comparisons such as quantitative information will be analyzed using analysis of variance or Wilcoxon rank sum test. Categorical data will be analyzed by chi-square test or exact probability method, while hierarchical information will be assessed through rank sum Wilcoxon test or CMH test. The significance level for each test will be set at *P* < 0.05.

The MRI pre-processing will be conducted using the data processing assistant for Rs-fMRI, which operates in conjunction with the statistical parametric mapping software (SPM82). Subsequently, the EEG data will undergo offline processing through MATLAB software scripts and the EEGLAB toolbox.

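### Three PDQ-39 visits share primary status at 0.05 per test, with no primary visit and no rule for which visit or visits must succeed

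*Protocol article*

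**What the plan says.** The Primary outcome measures part of Outcomes {12} states: "The primary outcome indicator will be the PDQ-39, which assesses changes in quality of life from T0 to T2, T3, and T4". The Methods paragraph of the abstract lists the same three visits. Neither place ranks them, and neither says how results at the three visits combine into one conclusion.

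The same part of Outcomes {12} says that the scale yields "a comprehensive index score, eight sub-core scores, and a weighted percentage reflecting problem severity". It does not say which of these is the primary variable.

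Statistical methods {20a} describes the primary analysis as follows: "an analysis of covariance (ANOVA) model will be employed to estimate the adjusted means of" the quality-of-life scores, with adjustment for baseline and a 95% confidence interval for the difference between arms. No visit and no PDQ-39 score is attached to that model. The section closes with "The significance level for each test will be set at" P < 0.05.

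Sample size {14} states: "The statistical power was set at 0.9, with a significance level (α) of 0.05". It arrives at 27 per group, raised to 30 for 10% attrition, and does not mention three primary comparisons.

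The one multiplicity provision is in Methods for additional analyses {20b}: post hoc t-tests, Bonferroni corrected, comparing assessment time points for every outcome variable.

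**The concern.** Three visits of equal primary standing, each tested at 0.05, leave room to decide after the data are seen which visit carries the trial. The Discussion says the trial is meant to confirm both efficacy and lasting benefit for quality of life. Without a rule, a single nominal P < 0.05 at 4, 12 or 24 weeks could be presented as that confirmation. A result significant at one visit and not at the other two could be called positive or negative with equal support from the text.

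This is more than silence that an analysis plan could fill. The article states a rule, 0.05 for each test, alongside three listed primary visits. An analysis plan would have to alter that rule or add a decision structure that the article lacks.

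**Working it through.** **Inputs from the article.** Three primary visits, T2, T3 and T4 (Abstract; Outcomes {12}). Per-test level 0.05 (Statistical methods {20a}). Design alpha 0.05, power 0.90, 27 per group, 10% attrition, 30 per group (Sample size {14}).

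**Assumed, because the article does not give them.** Two-sided tests, approximately normal test statistics, and a common correlation ρ between the statistics at the three visits.

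**1. The plan's own sample size.** The attrition step reproduces: 27 / (1 − 0.10) = 30. The 27 itself cannot be recomputed, since no difference or SD is stated. Solving backwards for the standardised difference d:

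- Two-sided, normal approximation: d = √(2/27) × (1.960 + 1.282) = 0.88. The t-test version gives 0.90.
- One-sided: 0.80 (normal) or 0.81 (t).

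Each calculation is for one comparison at the full 0.05.

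**2. Error rate if any one visit is enough.** For independent statistics, 1 − (1 − 0.05)³ = 1 − 0.857375 = 0.143. The Bonferroni upper bound is 3 × 0.05 = 0.15. For a common correlation ρ > 0, with c = 1.960,

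FWER = 1 − ∫ [Φ((c − √ρ·x)/√(1−ρ)) − Φ((−c − √ρ·x)/√(1−ρ))]³ φ(x) dx

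| ρ (assumed) | FWER |
|---|---|
| 0 | 14.3% |
| 0.3 | 13.6% |
| 0.5 | 12.5% |
| 0.7 | 10.9% |
| 0.8 | 9.8% |
| 0.9 | 8.4% |

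This is 8.4/5 = 1.7 to 14.3/5 = 2.9 times the nominal level.

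**3. Error rate if all three visits must succeed.** A false claim then needs a false rejection at every visit where there is no effect, so its probability is at most 0.05. Alpha holds without adjustment. Power is what suffers: if each visit had 90% power, joint power would lie between 0.9³ = 72.9% (independent) and 90% (perfectly correlated).

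**4. If the Bonferroni wording were meant for the primary test.** The level would be 0.05/3 = 0.0167 per visit, with FWER 1 − (1 − 0.0167)³ = 4.9% under independence. At 27 per group and the implied two-sided d, power at one visit is Φ(0.8822 × √(27/2) − 2.394) = Φ(0.848) = 80%, or 79% by the t-test. Restoring 90% needs 2 × (2.394 + 1.282)² / 0.8822² = 34.7, so 35 per group, and 35/0.9 = 38.9, so 39 after attrition. That reading would therefore conflict with Sample size {14}, which has no such allowance.

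**The case against.** **The any-visit rule is not written down.** This is correct. The article neither states nor excludes it, so a reader who infers that the trial's 5% error rate is definitely lost goes further than the text. The supportable statement is conditional: the decision rule is undefined, and one natural reading inflates the error.

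**There is a Bonferroni provision.** It covers all outcome variables, which include PDQ-39, so it would be wrong to say that the document has no multiplicity wording. But it is placed under additional analyses, is labelled post hoc, uses t-tests, and reads most naturally as comparing time points. The primary analysis is a baseline-adjusted comparison between arms. Nothing links the two or overrides the 0.05 set for each test.

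**The analysis plan may settle it.** An article condenses, and an order of testing is often set elsewhere. This limits the point to what the article does fix: three primary visits and 0.05 for each test.

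**Stronger readings that the article does not support.** A reader might multiply nine PDQ-39 scores (the index and eight domains) by three visits and count 27 primary tests. The article only describes what the scale produces; it does not say that the domains are primary or will each be tested. It also gives a single 0 to 100 range and one pair of clinical thresholds, which fits one overall score. What stands is that the primary score is not named. Adding up error over the secondary scales is also unwarranted, since no confirmatory secondary claim is stated.

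**Conclusion.** The point holds in conditional form. The primary outcome spans three visits with no primary visit and no success rule, each test is set at 0.05, and the sample size spends one alpha of 0.05. If any one visit counts as success, the family-wise error is about 8% to 14%, for assumed correlations from 0.9 to 0 and two-sided tests; every value in that range exceeds 5%. If all three visits were required, alpha would hold, with lower power than stated unless the visits were perfectly correlated. The article does not choose between these readings. It should do so before unblinding, because the choice determines what a positive trial is.

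A separate, minor inconsistency: the abstract gives MDS-UPDRS III as the secondary outcome and adds "Additional clinical assessments and mechanistic studies were conducted as tertiary outcomes", whereas Outcomes {12} lists six scales as secondary. This does not affect the primary error rate.

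**What to change.** Before unblinding:

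- Name change from baseline in the PDQ-39 summary index as the single primary variable, and treat the domain scores as supportive.
- Either name one primary visit, or pre-specify a fixed order of testing over T2, T3 and T4 at two-sided 0.05, stopping at the first non-significant result. The sponsor should choose the visit or the order to match its main claim, whether early benefit or durability. The article gives no visit-specific attrition or effect figures that would favour one order.
- State in Statistical methods {20a} that the 0.05 level applies within this structure, and in {20b} that the Bonferroni correction concerns only the post hoc comparisons.
- Make the abstract and Outcomes {12} agree on which scales are secondary and which tertiary.

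The cost is about a paragraph of text. N stays at 30 per group, and the first test keeps its planned power. The downside of a fixed order is that claims at visits later in the order depend on success at those before them; with one primary visit, the other two become supportive.
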